### Recruitment {15}

Recruitment for our trial targets pregnant individuals diagnosed with HDP who are attending our hospital’s high-risk maternal care center. Screening for eligibility criteria is conducted by the attending obstetrician, who verifies whether the patients meet the specified criteria. Patients receive a comprehensive explanation of the trial’s risks and benefits to ensure their full understanding before being asked to provide voluntary written consent for participation. This process aims to ensure that participants are fully informed and willing to enroll in the study.

## Assignment of interventions: allocation

### Sequence generation {16a}

In this study, the allocation sequence was generated using SAS version 9.4 (SAS Institute, Cary, NC, USA) software. The allocation sequence was implemented and managed in the web-based case report form (CRF) system provided by GoodResearchUS (Seoul, Korea), where system roles and access permissions are established. Stratified permuted-block randomization was employed to ensure balanced assignment of subjects to each group. Block sizes were determined as multiples of 2 (e.g., 2, 4, 6). These blocks were generated using stratified randomization, with medication adherence as a stratification factor. Upon patient enrollment, the web-based CRF system generates a randomization table, automatically assigning participants to either the intervention or control group. This process is centrally managed, and allocation information is disclosed to participants immediately after group assignment.

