### Eligibility criteria {10}

#### Inclusion criteria

Our prospective study plans to enroll 580 pregnant individuals who meet one of the following criteria for HDP [13].Chronic hypertension, defined as diagnosed hypertension within the first 20 weeks of gestation (elevated office or clinic blood pressure ≥ 140/90 mmHg) or ongoing antihypertensive medication usageGestational hypertension which involves pregnant individuals newly diagnosed with hypertension after the 20 weeks of gestation (elevated office or clinic blood pressure ≥ 140/90 mmHg) or those receiving antihypertensive treatment.Preeclampsia, characterized by new-onset hypertension after 20 weeks of gestation (elevated office or clinic blood pressure ≥ 140/90 mmHg) along with concurrent indicators such as proteinuria, thrombocytopenia, abnormal renal function, elevated liver enzymes, neurological symptoms, and pulmonary edema.Superimposed preeclampsia in pregnant individuals diagnosed with hypertension within 20 weeks of gestation or those on antihypertensive medication who experience symptoms or signs associated with this condition.Individuals with a heightened risk of pregnancy-related hypertension due to factors such as multiple pregnancies, obesity, diabetes, or a history of hypertension-related disorders in prior pregnancies leading to preterm birth.Prospective participants should be 18 years or older, possess a smartphone, be capable of using applications, and be proficient in the Korean language.

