## Interventions

### Explanation for the choice of comparators {6b}

The participants follow the 2022 Korean Hypertension Treatment Guidelines [14]. These guidelines recommend ambulatory blood pressure monitoring for pregnant individuals with hypertension to avoid unnecessary medication. Pharmacological treatment is initiated for severe hypertension (≥ 160/110 mmHg), aiming to lower blood pressure below 150/100 mmHg without reducing diastolic pressure below 80 mmHg excessively. Postpartum, efforts are made to maintain blood pressure below 140/90 mmHg. The choice of medication considers prior usage, side effects, and fetal risk.

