### Strategies to improve adherence to interventions {11c}

Adherence in this study is determined by the frequency of blood pressure measurements and the regularity of logging into the Heart4U application in the intervention group. The study team monitors adherence during clinical visits scheduled for antenatal examinations. To enhance adherence, the research nurse conducts regular assessments during clinical visits, ensuring that participants encounter no difficulties with using the blood pressure monitor and the application. Additional education is provided as needed to address any challenges and optimize participant engagement with the intervention.

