#### Secondary outcomes

Trajectory blood pressure: Throughout the study duration, trajectories of systolic, diastolic, and mean blood pressure will be tracked.Obstetric outcomes: This includes but is not limited to:Antihypertensive medication useProgression to severe preeclampsia or eclampsiaPulmonary edemaFetal growth restrictionOligohydramniosPreterm placental abruptionPreterm delivery (between 20 and 37 weeks)Miscarriage (before 20 weeks)Fetal demiseNewborn weightLow birth weightPostpartum hemorrhage (including transfusion)Trajectory of body mass index (BMI): analysis of BMI trajectory.Physical activity monitoring: step counts recorded through Samsung Health or iPhone-Health applications.Depressive Mood Assessment: depressive symptoms will be assessed using surveys, including the Patient Health Questionnaires-9 and Beck Depression Inventory [15, 16], administered at enrollment and at the conclusion of the study. These tools are widely recognized and validated measures for evaluating depression symptoms and severity.Drug adherence: evaluation of medication adherence through pill counts

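### The named stratification factor, medication adherence, has no value at enrolment for eligible women on no antihypertensive, so the strata cannot be formed for every participant as written

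*Protocol article*

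**What the plan says.** Sequence generation {16a} describes stratified permuted blocks and names one factor: "These blocks were generated using stratified randomization, with medication adherence as a stratification factor". On timing, the same section says: "Upon patient enrollment, the web-based CRF system generates a randomization table, automatically assigning participants to either the intervention or control group". It gives no levels, cut-off, reference period or instrument for the factor.

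Four other places bear on what the factor could mean:

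- Secondary outcomes lists "Drug adherence: evaluation of medication adherence through pill counts".
- Strategies to improve adherence {11c} uses the word differently: "Adherence in this study is determined by the frequency of blood pressure measurements and the regularity of logging into the Heart4U application", the log-ins applying to the intervention group.
- Inclusion criteria admits, besides the diagnosed disorders, "Individuals with a heightened risk of pregnancy-related hypertension due to factors such as multiple pregnancies, obesity, diabetes" or a relevant obstetric history. It also admits women already on antihypertensive treatment in the chronic hypertension, gestational hypertension and superimposed preeclampsia categories.
- Explanation for the choice of comparators {6b} says of standard care: "Pharmacological treatment is initiated for severe hypertension", with a threshold of 160/110 mmHg. A diagnosis qualifies for entry at 140/90 mmHg.

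Statistical methods {20a} names two-sample t-tests or Mann–Whitney tests for continuous outcomes and mentions no covariates.

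**The concern.** A stratification factor must have a known value for every participant before she is allocated. The factor named here shares its label with an outcome collected during follow-up, and it has no meaning for a woman who takes no drug. If the text is followed literally, someone must place untreated women in a stratum without a rule.

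At stake are the balance that stratification is meant to give, the precision gained by adjusting for a well-defined stratifier, and the ability to describe the randomisation accurately in the final report. The matter is current: Trial status says recruitment opened in September 2023 and is expected to run to August 2026, so strata may already have been assigned on a variable that the article does not define.

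**Working it through.** **Can each possible meaning of the factor be evaluated at enrolment?** The reading throughout is that medication means antihypertensives, the only drug treatment the article describes.

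1. *In-trial adherence by pill count* (the secondary outcome). It is not available at enrolment for anyone, and the intervention may affect it.
2. *Adherence as described in section {11c}* (frequency of blood pressure measurement, app log-ins). It arises after allocation, and log-ins exist in one arm only. It is not medication adherence.
3. *Adherence before enrolment.* It can exist for women already treated. It is undefined for women on no drug unless they have a level of their own, and none is stated.
4. *Antihypertensive use at enrolment.* It is defined for everyone, but it is not what the text says.

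Only the fourth reading, or the third with an added level for untreated women, gives every participant a stratum. The article states neither.

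**Are untreated women really expected?** Yes, by two routes. Women may enter on risk factors alone. A woman may also enter with a new diagnosis at 140/90 mmHg, while drug initiation under the cited standard care is tied to 160/110 mmHg. The second route remains even if recruitment is confined to diagnosed disease, as Recruitment {15} suggests. Intervention description {11a} adds that new prescriptions may follow after enrolment. The article does not give the share untreated at enrolment.

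**Does the sample size depend on the factor?** Inputs from Sample size {14}: difference 3.2 mmHg, SD of the change 13 mmHg, alpha 0.05 (two-sided, from Statistical methods {20a}), power 80%, dropout 10%.

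- Normal approximation: n = 2 × [13 × (1.960 + 0.842) / 3.2]² = 259.07, rounded up to 260 per arm.
- t distribution: 260.04, rounded up to 261 per arm, which is the stated figure.
- Total 2 × 261 = 522, and 522 / (1 − 0.10) = 580, as stated.

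This is an unstratified two-group calculation, so the choice of stratifier does not change it.

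**How much balance is at issue?** Suppose a binary baseline factor with prevalence p is not balanced by stratification. With 290 per arm, the 95% range of the between-arm difference in proportions is ±1.96 × √[p(1 − p) × 2/290]. The prevalences are assumed:

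- p = 0.10: ±4.9 percentage points
- p = 0.30: ±7.5 percentage points
- p = 0.50: ±8.1 percentage points

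As an illustration, take a factor whose two levels differ in SBP change by as much as the target effect, 3.2 mmHg. The arm difference would then shift by at most about 0.049 × 3.2 = 0.16 mmHg to 0.081 × 3.2 = 0.26 mmHg over this range. The shift scales with the strength of the factor. It is ordinary chance variation and not a systematic error.

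**The case against.** The best defence is that a shared label does not make the stratifier the follow-up outcome. A variable can be measured at baseline and again later. Several entry categories include women already on treatment, including some with gestational hypertension, so a pre-enrolment value can exist for part of the sample. A version with a level for women not on medication would be workable, and the full protocol or the vendor's specification, neither of which is shown, may define it. This stands as far as it goes: it cannot be said that no valid strata exist. It does not rescue the text, because the article names a factor that some eligible women cannot have and nothing in it says how they are classified. That is a stated rule that does not work for everyone, and so more than a missing detail.

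A reader might infer four stronger things, none of which the article supports:

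- *The randomisation is biased, or staff can steer allocation through the choice of stratum.* Concealment mechanism {16b} describes central web-based assignment from an undisclosed table. Misplacing a woman in a stratum before a concealed 1:1 assignment weakens balance but does not favour an arm.
- *The factor balances nothing prognostic.* Nothing shows this. Pre-enrolment adherence, or the treatment status it implies, could relate to SBP.
- *The share of untreated women can be read off the planning values.* With mean 146 and SD 13, about 14% of enrolment SBPs reach 160 mmHg. This ignores the diastolic limb, women already treated and prescribing at the physician's discretion, so it does not estimate the untreated share.
- *The standard error of the baseline SBP difference, 13 × √(2/261) = 1.14 mmHg or 36% of 3.2 mmHg, measures the harm.* Because the SD of the change is also set at 13, this equals the standard error already built into the sample size. It is not extra error from a poor stratifier.

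It is also fair to say that covariates are often left to the analysis plan and that leaving a stratifier out of the analysis is typically conservative. The absence of covariates in section {20a} is therefore a secondary matter.

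**Conclusion.** The point holds in this form: as written, the stratification cannot be carried out for all participants, because the named factor coincides with a pill-count secondary outcome and is undefined at enrolment for eligible women on no antihypertensive. The consequence is some loss of balance and precision, and a randomisation method that cannot be reproduced from its description. Validity of the concealed 1:1 comparison and the sample size of 580 are not affected.

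The size of the loss cannot be calculated from the article, which gives neither the share untreated nor the prognostic strength of treatment status. The 5 to 8 percentage points of chance imbalance rest on assumed prevalences and indicate scale only. The conclusion would change if the full protocol or the vendor's configuration defined a baseline variable with a level for untreated women. The defect would then be one of wording.

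**What to change.** First establish from the vendor what the system records as the stratum, including for women on no drug.

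- If it records antihypertensive use at enrolment, or pre-enrolment adherence with a level for women not on medication, correct Sequence generation {16a} to state the variable, its levels and its time point.
- If it records anything else, amend for remaining participants to a factor known for everyone before allocation, such as antihypertensive use at enrolment (yes/no). Document the strata used so far as they were, without relabelling them.

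In either case, include the factor actually used and baseline antihypertensive use as covariates in the primary SBP analysis, and keep the baseline factor distinct in name from the pill-count outcome and from the adherence described in section {11c}.

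The cost is a short amendment, and possibly a vendor configuration change that leaves different factors in force before and after it. Covariate adjustment handles that change.

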### Concealment mechanism {16b}

Random allocation is achieved using a centralized, web-based randomization system based on a pre-prepared randomization table. The randomization table is not disclosed to the researchers and is securely stored in the web-based CRF database managed by the vendor. Upon participant registration, the randomization table generation function automatically assigns participants to either the intervention or control group. This process rigorously conceals the allocation sequence to ensure the reliability of the study. Allocation information is disclosed to participants only immediately after group assignment, maintaining allocation concealment throughout the study.

### Implementation {16c}

Enrollment of participants will be conducted by sub-investigators, including obstetric physicians who are blinded to the allocation. The randomization module will be utilized to assign participants without disclosing the complete allocation scheme. This approach ensures that the enrollment process remains unbiased and maintains the blinding of both participants and investigators throughout the study.

## Assignment of interventions: blinding

### Who will be blinded {17a}

Blinding of the participants is not feasible due to the nature of the intervention in this trial. Additionally, the attending physicians cannot be blinded as they need to share blood pressure monitor data and provide feedback to patients in the intervention group. However, outcome assessors will be blinded to ensure that their assessments do not influence the analysis results.

### Procedure for unblinding if needed {17b}

The design is open label with only outcome assessors being blinded so unblinding will not occur.

## Data collection and management

### Plans for assessment and collection of outcomes {18a}

For the assessment and collection of outcomes, baseline information will be collected by trained research nurses who will input the data into a web-based CRF at the time of study registration. Both groups will receive an OMRON blood pressure monitor, with the standard care group having their self-measured blood pressure automatically entered into the OMRON application via Bluetooth. In contrast, the group using Heart4U will have their measured blood pressure automatically synchronized with the application. The synchronized data will be seamlessly integrated with the web-based CRF, eliminating the need for additional data collection. Any errors or discrepancies in the data will be managed by an independent data committee, which is designed to notify stakeholders of any incorrect values.

### Plans to promote participant retention and complete follow-up {18b}

Participants in this study have the autonomy to withdraw from the research at any point without facing any obligation to complete the study. As a pragmatic trial grounded in real-world settings, there is no compulsion for participants to fulfill additional follow-up requirements beyond their routine antenatal examinations and the standard postpartum outpatient visit scheduled 1 month after childbirth. Given that data collection aligns with participants’ regular antenatal examination schedules and the final follow-up coincides with the typical postpartum outpatient visit, we anticipate minimal participant burden and expect the dropout rate to be low. This approach aims to integrate the research seamlessly into participants’ existing healthcare routines, promoting retention and adherence throughout the study duration.

### Data management {19}

In our study, we utilize a web-based CRF system to facilitate direct digital data entry, standardize data collection processes, and automate data management. This approach enhances the accuracy of data, reduces input errors, and streamlines data processing time. Additionally, our system incorporates automated queries within the web-based CRF to identify and address missing data or inconsistencies, ensuring data integrity.

Following data collection, we perform thorough data validation and cleaning processes to review the consistency, accuracy, and safety of the data. Continuous access to the web-based CRF and Excel files allows for ongoing data review and potential modifications as needed. This iterative process ensures the quality and reliability of the data throughout the study duration. Overall, our data management approach ensures standardized, efficient, and secure handling of data, ultimately contributing to the quality assurance of our study outcomes.

### Confidentiality {27}

All people involved in the study are subject to confidentiality. All data will be collected and analyzed pseudonymously. Extensive measures will be taken to protect the data, especially personal data, against access by third parties. Local therapy files and study data will be stored in locked cabinets and will only be accessible to study staff and to the respective treating therapists who are subject to the legal duty of confidentiality. The data collected so far will further be used and analyzed within the study, unless participants withdraw their consent to processing their data as well. If a participant only discontinues the study treatment, but not participation in general, further data required for the study can be collected and used.

All therapists, supervisors, and study assistants are also subject to medical confidentiality. No information collected during the therapy will be passed on to third parties unless the participants give their explicit written consent.

### Plans for collection, laboratory evaluation, and storage of biological specimens for genetic or molecular analysis in this trial/future use {33}

Not applicable as no biological specimens will be collected.

## Statistical methods

### Statistical methods for primary and secondary outcomes {20a}

All continuous variables among the primary and secondary efficacy evaluation variables will be presented as mean and standard error or median and quartiles, and categorical variables will be summarized as percentages compared with the population parameters. Normally, two-sample *t*-tests or the Mann–Whitney *U* test, depending on whether the data follow a normal distribution, are used for continuous variables after assessing normality using the Kolmogorov–Smirnov test. The distributions of categorical variables are analyzed with *χ*^2^ tests or Fisher’s exact tests. The ITT principle will be used for all analyses. For each subgroup, we will calculate the hazard ratio and 95% confidence intervals for the primary and secondary endpoints. Statistical significance is set at a two-sided *P*-value of < 0.05. Statistical analyses will be performed using R version 4.3.1 (R Foundation for Statistical Computing, Vienna, Austria). The datasets analyzed in the current study will be available from the corresponding author upon request.

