### Outcomes {12}

#### Primary outcome

The primary endpoint of this study is the difference in SBP measured between the point of enrollment and the conclusion of the study, which is 1 month ± 1 week after childbirth.

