### Sample size {14}

The determination of the sample size for this study, with an intended enrollment of 580 participants, was established using specific parameters as follows [17, 18]: the mean SBP at the point of enrollment was 146 mmHg, accompanied by a standard deviation of 13 mmHg. Subsequently, the mean SBP 1 month after childbirth was projected to be 130 mmHg, with a corresponding standard deviation of 12 mmHg. The control group displayed a delta SBP of 16 mmHg, whereas the delta SBP of the intervention group was amplified by 20% to 19.2 mmHg. The required difference between the two groups for sample size computation was 3.2. Moreover, a standard deviation of 13 mmHg was attributed to the delta SBP. These considerations are further coupled with an alpha error of 0.05 and a power of 80%. Using these variables, the calculations stipulated the necessity of 261 participants within each group, culminating in a total of 522. Considering a presumed dropout rate of 10%, the required comprehensive sample size was 580 participants.

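### The primary SBP comparison is an unadjusted test picked by a normality pretest; adjusting for enrolment SBP would raise power from 80% to about 93% on the SDs given

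*Protocol article*

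**What the plan says.** The Primary outcome section of the Protocol article reads: "The primary endpoint of this study is the difference in SBP measured between the point of enrollment and the conclusion of the study", which falls one month after childbirth, give or take a week. Enrolment SBP is therefore recorded for every participant as part of the endpoint.

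Statistical methods for primary and secondary outcomes {20a} opens with "All continuous variables among the primary and secondary efficacy evaluation variables", so its rules reach the primary endpoint. The tests named are the two-sample t-test and the Mann–Whitney U test, which, "depending on whether the data follow a normal distribution, are used for continuous variables after assessing normality" with a Kolmogorov–Smirnov test. The section names no baseline value or other covariate, and no other section does either.

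Sample size {14} rests on a difference in mean change. An SD of 13 mmHg "was attributed to the delta SBP", the target difference is 3.2 mmHg (19.2 against 16), and 261 per arm is the result.

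Sequence generation {16a} adds: "Stratified permuted-block randomization was employed to ensure balanced assignment of subjects to each group". The one stratification factor named there is medication adherence.

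**The concern.** There are two separate issues.

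**Precision.** Change from baseline is correlated with baseline. A participant who enrols with a high reading tends to fall further whichever arm she is in. An unadjusted test on change leaves that variation in the error term, and a chance difference in enrolment SBP between arms passes into the estimate. Regression on enrolment SBP removes both at no cost in data.

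**An unfixed primary test.** Which hypothesis is tested depends on a normality test applied to the trial's own data. If Kolmogorov–Smirnov rejects, the primary analysis becomes a rank comparison with no estimate in mmHg, although the trial was sized on a mean difference. With about 260 per arm, comparing means does not require normally distributed raw data, so the pretest protects little. Its power to reject harmless departures also grows with sample size.

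At stake are a sizeable margin of power and a primary result whose meaning is settled before the data are seen.

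**Working it through.** **Inputs, all from Sample size {14} unless noted.** At baseline, "the mean SBP at the point of enrollment was 146 mmHg, accompanied by a standard deviation of 13 mmHg". One-month SBP: mean 130, SD 12. SD of change 13. Difference 3.2. Alpha 0.05 (two-sided, from {20a}), power 80%, 261 per arm.

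**Step 1: reproduce the plan's figure.** n per arm = 2(1.96 + 0.842)² × 13² / 3.2² = 259.1, which rounds up to 260. The t-based solution is 260.04, which rounds up to the stated 261. Then 2 × 261 = 522 and 522 / 0.90 = 580. All three stated figures reproduce.

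**Step 2: power of the unadjusted test.** SE = 13 × √(2/261) = 1.138. 3.2 / 1.138 = 2.81. Power = Φ(2.81 − 1.96) = 80.3% (80.1% with the t distribution).

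**Step 3: the implied correlation.** The variance of a change is s₀² + s₁² − 2·r·s₀·s₁, so r = (169 + 144 − 169) / (2 × 13 × 12) = 144 / 312 = 0.46.

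**Step 4: power of ANCOVA.** Residual SD = 12 × √(1 − 0.4615²) = 10.65. Variance ratio to the change score = 113.3 / 169 = 0.67. SE = 10.65 × √(2/261) = 0.932. 3.2 / 0.932 = 3.43. Power = Φ(3.43 − 1.96) = 93.0% (92.9% with the t distribution). In 4,000 simulated trials with normal data, power was 92.8% for ANCOVA, 80.8% for the t-test on change and 79.1% for Mann–Whitney. ANCOVA would reach 80% power with 174 per arm.

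**Step 5: vary the correlation.** SDs of 13 and 12 are held, so the SD of change moves with r:

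| r | SD of change | ANCOVA residual SD | Power, change | Power, ANCOVA |
|---|---|---|---|---|
| 0.3 | 14.81 | 11.45 | 69% | 89% |
| 0.4 | 13.72 | 11.00 | 76% | 91% |
| 0.46 (implied) | 13.00 | 10.65 | 80% | 93% |
| 0.5 | 12.53 | 10.39 | 83% | 94% |
| 0.6 | 11.22 | 9.60 | 90% | 97% |

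Moving each of the three SDs by ±0.5 mmHg gives ANCOVA power of about 90% to 96%. The direction does not depend on r. The change-score variance exceeds the ANCOVA residual variance by (s₀ − r·s₁)², here (13 − 5.54)² = 55.7 = 169 − 113.3. With SDs of 13 and 12 this is always positive.

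**Step 6: chance imbalance.** One standard error of the baseline difference is 13 × √(2/261) = 1.14 mmHg. The regression slope is 0.4615 × 12/13 = 0.426. An imbalance of that size moves the change-score estimate by (1 − 0.426) × 1.14 = 0.65 mmHg, about 20% of the 3.2 target.

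**The case against.** The strongest reply is that nothing stated is incorrect. Endpoint, sample size and t-test agree with one another, the comparison is unbiased over randomisation, and the trial has the power it claims. That stands. A reader might infer that the primary test is invalid or the trial undersized; the documents support neither.

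A second reply is that covariate adjustment is often left to an analysis plan, which is not shown, and that {20a} is a generic paragraph with a hedged opening. This carries some weight, but the article does name the tests and the rule for choosing between them. The point is about a stated choice, not an omission.

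Third, the pretest may seldom matter. In a simulation with normal data, 261 per arm and an ordinary Kolmogorov–Smirnov test on pooled, arm-centred values, the switch occurred in under 0.1% of trials, with type I error 4.9% and power 80.5%. That also stands for those assumptions; non-normal data or a Lilliefors correction would trigger it more often. What remains is that the fallback does not address the quantity the trial was sized on.

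Two further readings go too far. A reader might say that ignoring the stratified randomisation makes the standard errors misleading. If the factor is prognostic, the unadjusted test is conservative, and the article does not show that it is prognostic. A reader might also attach power figures to the mix of hypertensive and at-risk participants admitted by the inclusion criteria. The article gives no share, mean SBP or expected effect for the at-risk group, so such figures would rest on invented inputs and none are given here.

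**Conclusion.** The concern holds as a loss of efficiency together with an unfixed primary test. It is worth correcting but does not threaten the trial's validity. On the three SDs given, the residual variance falls by a third and power at 261 evaluable per arm rises from 80% to about 93%.

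The 93% should not be read as exact. The correlation of 0.46 is implied by the SDs and stated nowhere, and the SD of change equals the baseline SD, so it may have been carried over. Correlations from 0.3 to 0.6 give ANCOVA 89% to 97% against 69% to 90% for the change score. All these figures assume that the stated SDs and the 3.2 mmHg difference hold for the participants actually enrolled.

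**What to change.** Name a single primary analysis in {20a}: linear regression (ANCOVA) of one-month postpartum SBP on arm and enrolment SBP, reporting the adjusted mean difference in mmHg with a 95% confidence interval. The endpoint definition can stay. Regressing the change on the same terms gives the identical arm coefficient, and the target remains the mean difference of 3.2 mmHg.

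Add the randomisation stratification factor as a covariate, using its value as recorded at randomisation. The text should say what that value is: {16a} calls it medication adherence without defining it at baseline, and the Secondary outcomes section measures drug adherence by pill counts as an outcome. A value measured after randomisation must not enter the model.

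Delete the Kolmogorov–Smirnov switching rule for the primary endpoint and keep Mann–Whitney only as a sensitivity analysis.

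The cost is wording; no new data or participants are needed. The design is open-label and Trial status puts the end of recruitment at August 2026 and completion at June 2027, so the change should be dated and recorded before any comparison of outcomes by arm.
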